### Participant timeline {13}

Study participants undergo eligibility screening and informed consent prior to taking part in the baseline assessment. Baseline must occur within 28 days of screening; otherwise, the participant must be re-screened to ensure continued eligibility. Once the baseline assessment is complete, randomisation occurs. The study interventionist assigned to the case communicates directly with the participant about their treatment assignment and schedules the first session. Participants are given 12 weeks after randomisation to complete all intervention sessions, which provides a realistic window to complete the intervention. The blinded research assistants conduct the follow-up assessments for each participant at 8 weeks (range 6–16 weeks), 20 weeks (range >16–28 weeks), and 32 weeks (>28–40 weeks) after randomisation. Table 1 displays the schedule of study procedures and Fig 1 displays the study flow.

**Fig. 1 Fig1:**
[figure not shown]
Flow chart of the trial

### Sample size {14}

The sample size calculation to conduct a fully powered trial was informed by a meta-analysis of 22 randomised controlled trials evaluating digital psychological interventions in LMICs [18]. The meta-analysis found an average effect size of Hedge’s *g* = 0.60 in favour of the digital intervention, *g* = 0.53 for interventions addressing substance use, and *g* = 0.43 when an active control group was used. We therefore assumed a more conservative effect size of *g* = 0.40 in favour of mhGAP-Remote to calculate the sample size. This translates to a true mean difference of 2.4 points in the AUDIT score change between treatment arms from baseline to 8 weeks (range 6 to 16 weeks) follow-up. We assumed a pooled standard deviation (SD) of 6 [38, 39]. Thus, with an allocation ratio of 1:1, a sample size of 99 participants in each treatment arm is required for statistical power of 80% and a two-sided type I error of 0.05. Prior clinical trials by the study team within similar settings and populations (clinic-based recruitment, unhealthy alcohol use) indicate a roughly 10% attrition rate [36, 40]. However, we chose a more conservative estimate of 20% attrition resulting in a total sample size of *N*_planned_ = 248 (*n* = 124 per treatment arm). Prior to recruiting participants into the fully powered trial, we plan to pilot the study procedures with up to 10 participants.

### Recruitment {15}

Participants are recruited into the study from hospitals and nurse-led health centres in Butha-Buthe district. Patients undergoing general screening to enter the health facility (e.g., ongoing COVID-19 or tuberculosis screening) or those in the waiting areas are approached and verbal consent sought to ask screening questions. Prior to conducting formal screening, participants are told briefly about the study (e.g., treatment study for alcohol use in adults taking place over several months). Participants who are further interested are taken to a private space where the screening can be conducted. Recruitment fliers with study phone numbers, managed by research assistants and study coordinators, are posted in areas of high patient traffic where study staff are not based in order to actively advertise the study. Healthcare providers can also refer patients who they think would be eligible and interested.

## Assignment of interventions: allocation

### Sequence generation {16a}

After the baseline assessment, participants are randomly allocated to either the mhGAP-Remote or mhGAP-Standard intervention with an equal probability for assignment to each condition using an allocation table that was uploaded to REDCap. Block randomisation was conducted and stratified by sex (male vs. female) and age (< 50 years vs. ≥ 50 years). Sex was chosen as a stratification factor due to established differences in the biological processing of alcohol in male vs. female bodies [41], which often translates into higher alcohol consumption levels in men than in women [42]. Age was also chosen as a stratification factor due to older adults typically having less comfort with technology [43], which is pertinent to the interventions under investigation.

### Concealment mechanism {16b}

The allocation table was prepared by an independent statistician not involved in the study. The randomisation is conducted in REDCap using this pre-specified allocation table, which prevents study staff from anticipating the allocation sequence.

### Implementation of the randomisation {16c}

The study coordinator, who is not involved in intervention delivery, utilises REDCap to randomise participants to intervention arms. Specifically, after the baseline assessment is complete, the study coordinator enters the participant’s ID number in REDCap, alongside the participant’s sex and age, and clicks “randomise” to reveal the participant’s allocation. The allocation cannot be changed after this step is complete. The study interventionist assigned to the participant then directly informs the participant about which treatment arm they have been allocated to and schedules the first intervention session.

## Assignment of interventions: Blinding

### Who will be blinded {17a}

Providers of the intervention and participants are not blinded to study arm allocation. The trained research assistants who conduct study assessments with participants are blinded to the study arm. The study statistician is not a member of the study team, and, thus, is blinded to study arm allocation until the dataset is closed and formal unblinding of the data takes place in  the process of data analysis.

### Procedure for unblinding if needed {17b}

There is no procedure for unblinding, as we do not foresee any reason (e.g., safety concerns) that would require blinded team members to be unblinded during the course of the study.

## Data collection and management

### Plans for assessment and collection of outcomes {18a}

Once a participant consents to study participation, self-reported assessments are collected in REDCap via interview. Trained research assistants collect dry blood spots (DBS) to assess for PEth, medical records are accessed to collect data on liver enzymes and HIV viral load (subsample with HIV only) and data is entered into REDCap. If participant medical records indicate a test result of more than 30 days old, research assistants escort participants to the medical staff to have new tests taken. All primary, secondary, and exploratory outcomes are collected at all timepoints (see {12} for description of outcomes).

Data quality is promoted by training assessors on adherence to data collection protocols and rules of trial conduct, including proper data collection techniques. Additionally, all members of the study team have completed formal human subjects research training in social and behavioural sciences, which is consistent with Good Clinical Practice. The AUDIT assessment is recorded and independent raters code randomly selected recordings to determine level of performance and adherence to assessment protocols.

### Plans to promote participant retention and complete follow-up {18b}

Our team has several strategies in place to promote retention to study assessments. To increase the likelihood of remaining in contact with participants throughout the study period, we collect primary contact information, including name, phone number, and preferred methods and times of contact. Additionally, the name, phone number, and relationship for two secondary contacts are also collected, in the event we cannot reach participants directly. The research assistant sends an SMS to the participant's phone after they have consented to the study and while they are still in the presence of the participant to ensure all participants can receive SMSs on their phone prior to randomisation. In addition, participants’ subsequent study-related assessment is scheduled prior to leaving their current visit. Participants also have the option of completing the self-report components of the assessments telephonically, to accommodate travels and migrant workers. Lastly, participants are compensated for their transport time and effort to attend assessment visits, with a range of 50 ZAR (~ 2.60 USD) to 150 ZAR (~ 7.80 USD) per assessment, depending on distance travelled.

### Data management {19}

Data is collected and managed using REDCap, a customisable electronic data collection and management software, hosted at the University Hospital Basel, Switzerland. All data is entered directly into the electronic forms on REDCap, thus creating an electronic Case Report Form (eCRF). All endpoint data is collected on the REDCap app and synced to the server when an internet connection is available. Hard copy data collection is used in the event of electricity failure or tablet malfunction. REDCap offers a secure database platform with validation tools to limit data entry errors by restricting entered values to those in plausible ranges as well as pop-up notifications confirming that decline to answer responses are not data entry errors [44, 45]. After data are synced to the server, a team member assigned to the task reviews the entire REDCap data record for completeness. Regular reports are run on the data to ensure accurate and complete data. A data clarification request is directed to the field team to address any missing or implausible data.

### Confidentiality {27}

All research-related data (except consent forms and study locator information) are coded using unique participant ID numbers. All research data are stored in a secure location with limited access. eCRFs are collected on password-protected study tablets via REDCap and data synced to the server as soon as an internet connection is available. Only trained study team members have access to the REDCap project containing participant data with unique personal login details. REDCap is compliant with the European Union’s General Data Protection Regulation [46]. When not in use, the tablets are stored in a locked cabinet within a locked room at the coordinating centre (see “Composition of the coordinating centre and trial steering committee {5d}”). Identifiable participant information (consent forms, locator information forms) are stored separately from research records in a locked cabinet in a locked room. Only the Lesotho-based research team has access to this information. The document linking participant IDs to participant names is password-protected and stored on a password-protected hard drive and backed up on a weekly basis. Only fully de-identified data will be made public. Audio recordings of intervention sessions and AUDIT assessments are stored on the study team’s Microsoft Sharepoint or a similar platform (hosted by the University Hospital Basel), which is only accessible to authorised study personnel.

### Plans for collection, laboratory evaluation and storage of biological specimens for genetic or molecular analysis in this trial/future use {33}

Liver enzyme results and HIV viral load are collected as part of routine clinical care in the health facility. If recent liver enzyme tests or HIV viral load tests (for subsample with HIV only) are unavailable, participants are referred for a routine test within the clinic from which they are recruited. DBS specimens for PEth are collected by trained study team members. After collection, DBS specimens are left to dry for up to 24 h. Dried samples are then placed in individual plastic bags with two desiccant bags and a moisture indicator cardboard. Once they have been prepared, they are stored temporarily in refrigerators within the laboratory of Butha-Buthe district hospital. On a bi-weekly basis, samples are transported in cooler boxes at 4°C for biobanking at Seboche laboratory until they can be shipped to a laboratory where analysis can take place. These samples are destroyed after processing is complete.

## Statistical methods

### Statistical methods for primary and secondary outcomes {20a}

Primary and secondary analyses will follow CONSORT guidelines and intention-to-treat principles (i.e., all participants will be analysed according to their randomisation condition, regardless of whether they complete the assigned treatment). A flowchart will describe the inclusion and follow-up of participants by study arm. Baseline characteristics will be described by study arm with summary statistics, such as mean and standard deviation for normally distributed data, median and interquartile range for non-parametric continuous data, or number and percentage in the case of categorical indicators. No formal testing between arms will be performed. Outcomes will be described by arm using summary statistics.

For the primary analysis, we will employ a linear regression model on the outcome of difference in mean AUDIT scores from baseline to 8 weeks follow-up (range 6–16 weeks) using the arm allocation, stratification factors, and site (if sample size per site allows). Only participants who have an AUDIT score at the 8-week assessment will be included in this analysis. Superiority of mhGAP-Remote will be demonstrated if the lower bound of the 95% Wald confidence interval of the difference between the arms is superior to zero.

We also plan, a priori, to conduct three separate sensitivity analyses on the primary endpoint. These are as follows:*Per protocol*. The per protocol analysis is defined as participants who attended at least one session of mhGAP-Standard or mhGAP-Remote. The per protocol analysis will allow for the evaluation of the intervention’s effects on participants who received at least a small dose of the treatment. Thus, only participants who completed at least one session of the intervention and who have an AUDIT score at the 8-week follow-up assessment will be included in this analysis. The analysis will then follow the primary analysis plan in using a linear regression model to predict difference in mean AUDIT scores from baseline to 8 weeks follow-up, using arm allocation, stratification factors, and site (if sample size allows) as independent variables.*Recovery*. If participants no longer meet the threshold of “hazardous drinking” at the 8-week follow-up assessment for alcohol use based on AUDIT score (< 6 for women, < 8 for men), they will be considered “recovered.” Otherwise, participants will be categorised as “non-recovered” because they continue to demonstrate a high burden of alcohol use symptoms. Rates of recovery will then be compared between mhGAP-Remote and mhGAP-Standard. Only participants with an AUDIT score at the 8-week follow-up assessment will be included in this analysis. For this analysis, we will employ a logistic regression model with recovery (yes/no) as the outcome and arm allocation, stratification factors, and site (if sample size allows) as independent variables.*Clinically significant and reliable change*. We will follow procedures outlined by Jacobson and Truax [47] for identifying clinically meaningful change in psychotherapy research. Means and standard deviations on the AUDIT from both clinical and non-clinical groups similar to the current population, based on a recent study in South Africa [48], will be used to establish the minimum amount of change needed that likely reflects true change in alcohol consumption (i.e., change that is not due to chance). Based on this calculation, a change of at least 8.4 points in the AUDIT score is the minimum required change. Participants would therefore need to decrease their total AUDIT score by 9 points to have clinically significant and reliable change. For this analysis, we will employ a logistic regression model with clinically significant and reliable change (yes/no) as the outcome and the same independent variables as in the primary analysis (i.e., arm allocation, stratification factors, and site [if sample size allows]).

For secondary analyses, we will evaluate changes from baseline in (1) AUDIT scores at the 20- and 32-week follow-ups and (2) changes in the biomarker PEth at 8-, 20-, and 32-week follow-ups. We will employ multilevel mixed effects regression models and control for clustering of variance within individuals over the repeated measures. For the AUDIT, we will use a normal distribution and identity link. For PEth, we will evaluate the data’s distribution and choose a suitable regression model and link function for analysis. Models will be adjusted for the arm allocation, stratification factors, and site (if sample size per site allows). We will report adjusted mean differences between treatment arms. Furthermore, we will compare the maintenance of “recovery” and clinically significant and reliable change at the 20- and 32-week follow-up assessments across the treatment arms.

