**Methods:**

This is a two-arm randomised open-label multicentre superiority trial. Participants allocated to mhGAP-Standard receive 4 in-person sessions using motivational interviewing, identifying triggers, and alternative behaviours, with the option of two additional booster sessions. Participants in the mhGAP-Remote arm receive 1 in-person session covering the same content, followed by standardised SMSs over 8 weeks that reinforce intervention content. Non-specialist providers deliver the intervention and receive weekly supervision. Adults (*N*_planned_ = 248) attending participating health facilities for any reason and who meet criteria for unhealthy alcohol use based on the Alcohol Use Disorders Identification Test ([AUDIT] score ≥ 6 for women, ≥ 8 for men) are individually randomised to the two arms (1:1 allocation, stratified by participant sex and age (≥ 50 vs < 50 years old). Follow-up assessments occur at 8, 20, and 32 weeks post-randomisation. The primary outcome is change in self-reported alcohol use (continuous AUDIT score), from baseline to 8 weeks follow-up. Change in the AUDIT from baseline to 20 and 32 weeks follow-up is a secondary outcome. Change in the biomarker phosphatidylethanol (secondary), liver enzyme values in serum (exploratory), and HIV viral load (for people with HIV only; exploratory) are also evaluated from baseline throughout the entire follow-up period. A linear regression model will be conducted for the primary analysis, adjusted for the stratification factors. Three a priori sensitivity analyses for the primary outcome are planned based on per protocol treatment attendance, recovery from unhealthy alcohol use, and clinically significant and reliable change.

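### The primary and per-protocol linear models analyse raw AUDIT change without baseline AUDIT as a covariate, giving up precision that costs nothing to recover

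*Protocol article*

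**What the plan says.** Under Statistical methods for primary and secondary outcomes {20a}, the primary analysis is a linear regression on the AUDIT difference from baseline to 8 weeks, "using the arm allocation, stratification factors, and site (if sample size per site allows". The abstract agrees: "A linear regression model will be conducted for the primary analysis, adjusted for the stratification factors". The per-protocol analysis follows the same model. The paragraph on clinically significant and reliable change repeats the independent variables of the primary analysis and introduces them with an i.e., so the list reads as complete. Sequence generation {16a} gives sex and age (below 50, or 50 and over) as the only stratification factors. Methods for additional analyses {20b} plans no further adjusted analyses among the main ones.

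Sample size {14} assumes an "effect size of *g* = 0.40 in favour of mhGAP-Remote", which it equates to "a true mean difference of 2.4 points in the AUDIT score change between treatment arms". It continues: "We assumed a pooled standard deviation (SD) of 6". With 1:1 allocation, "statistical power of 80% and a two-sided type I error of 0.05", this gives 99 per arm, and 248 in total after 20% attrition. The section does not say whether 6 is the SD of change or of the score at one visit, and it gives no correlation between baseline and follow-up.

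**The concern.** A raw change score fixes the slope of 8-week AUDIT on baseline AUDIT at 1. If the true slope differs from 1, the model leaves explainable variance in the residual. The article gives a reason to expect a slope below 1: its reliable-change calculation treats changes of less than 8.4 points as possibly due to chance, which implies considerable measurement error in a single AUDIT score, and such error pulls the slope down.

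What is at stake is precision. A wider confidence interval than necessary makes it harder to show a difference of the planned size, although the covariate that would narrow it is already collected. The unlabelled SD adds a second uncertainty. If 6 describes AUDIT scores rather than changes, the SD of change depends on a correlation the article does not give, and so does the power.

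**Working it through.** **Inputs from Sample size {14}.** Difference 2.4; SD 6; two-sided alpha 0.05; power 80%; 1:1 allocation; 99 evaluable per arm; 20% attrition. The correlation rho between baseline and 8-week AUDIT, and the separate SDs at the two visits, are not in the article. They are assumptions below, shown over a range.

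**Step 1: the plan's own figure.**
- n per arm = 2 × [6 × (1.960 + 0.842) / 2.4]² = 98.1, rounded up to 99.
- 99 / 0.8 = 123.75, rounded up to 124 per arm, 248 in total.
- Two-sample t-test power at 99 per arm with standardised difference 2.4 / 6 = 0.40 is 80.0%.

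The stated sample size is reproduced. All powers below are t-test powers at 99 per arm.

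**Step 2: general formulas.** Let SB and SF be the baseline and follow-up SDs.
- Variance of change = SB² + SF² − 2·rho·SB·SF.
- Residual variance with baseline as covariate = SF²(1 − rho²).
- Variance saved = (SB − rho·SF)². This is never negative, and it is zero only when the slope rho·SF/SB equals 1.
- If SB = SF, the ratio of adjusted to change-score variance is (1 + rho)/2.

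**Step 3: SD 6 is the SD of change, equal SDs at both visits.** The planned model has 80% power whatever rho is. The adjusted residual SD is 6 × √[(1 + rho)/2].

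| rho | residual SD | power with baseline AUDIT |
|---|---|---|
| 0.2 | 4.65 | 95% |
| 0.5 | 5.20 | 90% |
| 0.7 | 5.53 | 86% |
| 0.8 | 5.69 | 84% |

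At rho 0.5 the adjusted model would need 2 × [5.196 × 2.802 / 2.4]² = 73.6, so 74 per arm for 80% power. That is 93 per arm after attrition, or 186 in total against 248.

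**Step 4: unequal SDs.** Take SB = 5, SF = 6, rho = 0.5.
- Variance of change = 25 + 36 − 30 = 31.
- Adjusted variance = 36 × 0.75 = 27.
- Ratio 27/31 = 0.87, a 13% saving instead of 25%. If the SD of change is held at 6, power rises from 80% to about 85%.

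With SB = 5, SF = 7, rho = 0.6 the variances are 32 and 31.36, a saving of only 2%.

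**Step 5: SD 6 is a single-visit score SD, equal at both visits.** SD of change = 6 × √[2(1 − rho)]; adjusted residual SD = 6 × √(1 − rho²).

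| rho | planned change model | with baseline AUDIT |
|---|---|---|
| 0.2 | 60% | 82% |
| 0.3 | 66% | 84% |
| 0.5 | 80% | 90% |
| 0.7 | 95% | 98% |

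If the follow-up SD were 7 and the baseline SD 6, adjusted power would be 69% at rho 0.2 and 79% at rho 0.5. The change model would have 53% and 73%.

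**The case against.** The strongest objection is that nothing planned is invalid. Randomisation makes the change-score estimate unbiased, type I error is held, and the model matches both the declared outcome and the scale of the sample-size calculation. All of that stands: the point is about efficiency only.

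A reader might infer that the stated 80% power is unsupported because it rests on an unstated correlation. The article does not bear that out. It puts the 2.4 points on the change scale, and 2.4 / 6 gives the stated 0.40, so the plain reading is that 6 is the SD of change; 80% then holds at any correlation. Dependence on rho arises only under the other reading. The sources cited for the SD are not at hand to settle which is meant.

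Nor can one say that adjustment guarantees 80% at every correlation. That needs a follow-up SD of at most 6, and Step 5 shows it failing with a follow-up SD of 7. The size of the gain likewise depends on equal SDs. Entry is truncated at AUDIT 6 or 8 while follow-up is not, so a smaller baseline SD is plausible, and with it a smaller gain. That truncation is not itself a reason for a slope below 1: under a linear relation, selecting on baseline leaves the slope unchanged.

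Finally, the criticism does not carry over as the same omission to every model. Recovery is a status at 8 weeks, so no slope is forced on it. In the logistic models, adding baseline changes what the odds ratio is conditional on. For the mixed models ("Models will be adjusted for the arm allocation, stratification factors, and site") the article does not say whether baseline is among the repeated responses; if it is, it is already used.

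**Conclusion.** The concern holds for the primary and per-protocol linear models, as a loss of precision that should be recovered. The covariate list is fixed in the article and excludes baseline AUDIT. The adjusted model is, in large samples, never less precise, and it is equally precise only if the slope is exactly 1.

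Taking 6 as the SD of change and equal SDs at both visits, power at 99 per arm rises from 80% to between about 86% (rho 0.7) and 95% (rho 0.2). With a smaller baseline SD the gain shrinks, in an unfavourable case to almost nothing. The direction is certain; the size rests on assumed values of rho and the SDs.

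The sample-size arithmetic is correct. That the SD is not labelled is a secondary point. If it is a single-visit score SD, and the SDs are equal, the planned analysis falls short of 80% when rho is below about 0.5, which is a further reason to adjust.

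**What to change.** Add baseline AUDIT as a continuous covariate to the primary and per-protocol linear models, alongside arm, sex, age stratum and, where feasible, site. The estimated arm effect is then the same whether the outcome is change or the 8-week score, so the declared outcome need not change. Keep the raw-change model as a sensitivity analysis. In Sample size {14}, state whether 6 is the SD of change or of the score and, if of the score, the correlation assumed.

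The cost is a minor amendment to the protocol wording. The article requires ethics approval for amendments, and enrolment began in September 2023, so the change should be dated and in place before the data are unblinded. It needs no new data and no additional participants.

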### Methods in analysis to handle protocol non-adherence and any statistical methods to handle missing data {20c}

Previous clinical trials conducted by the study team have recorded less than 10% attrition [36, 40]. In the power analysis for the present study, we have used a conservative estimate of 20% attrition. Participants who drop out, who fail to attend a study assessment, or who are lost to follow-up will not be replaced by new participants, as we have accounted for this in the sample size estimate. Missing baseline and outcome data will be summarised by study arm and reported in the CONSORT. If attrition is higher than anticipated, multiple imputation will be used to impute the AUDIT score [50], and primary and secondary analyses will be conducted with the imputed datasets.

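### The primary analysis is complete-case unless overall attrition exceeds expectation, so outcome-related loss that differs by arm can bias the 8-week contrast with no correction and no sensitivity analysis

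*Protocol article*

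**What the plan says.** All of this comes from the protocol article.

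- **Principle.** Section {20a} adopts intention-to-treat, explained as: "all participants will be analysed according to their randomisation condition, regardless of whether they complete the assigned treatment".
- **Primary analysis set.** The same section then says: "Only participants who have an AUDIT score at the 8-week assessment will be included in this analysis". The model is a linear regression of AUDIT change on arm, the stratification factors and, where numbers allow, site. Baseline AUDIT is not among the listed covariates.
- **Missing data.** Section {20c} says: "If attrition is higher than anticipated, multiple imputation will be used to impute the AUDIT score". Otherwise missing data are only summarised by arm.
- **Anticipated attrition.** Section {20c} reports: "Previous clinical trials conducted by the study team have recorded less than 10% attrition". It continues: "In the power analysis for the present study, we have used a conservative estimate of 20% attrition". Section {14} says that the team's earlier trials "indicate a roughly 10% attrition rate".
- **Sensitivity analyses.** Section {20a} says: "We also plan, a priori, to conduct three separate sensitivity analyses on the primary endpoint". These are per protocol, recovery, and clinically significant and reliable change. The first two are expressly limited to participants with an 8-week score. The third states no handling of missing scores.

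**The concern.** These are rules the protocol states, not details left to a later analysis plan. Together they decide who is in the primary analysis, and they depend on the wrong quantity. Bias in a between-arm contrast comes from how loss relates to outcome and whether that differs between arms. The trigger looks only at how much is lost overall. A trial that loses 20% evenly and at random meets the rule, and so does one that loses 20% mostly from one arm and mostly among people still drinking heavily.

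The 20% figure is a sample-size allowance: it keeps about 99 per arm for power and says nothing about whether those 99 represent the 124 randomised. Because imputation is switched off in that range and no sensitivity analysis looks at missing outcomes, a reader of the results could not tell how far the finding depends on who came back.

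Differential loss is possible here. The arms differ in attendance burden (4 to 6 in-person sessions against 1), participants know their arm, and section {11a} acknowledges that distance and scheduling make weekly sessions difficult. Disengagement from treatment may carry over to assessments.

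**Working it through.** **1. Reproduce the design figures.** Section {14} gives a difference of 2.4 AUDIT points, SD 6, two-sided alpha 0.05, power 80% and 1:1 allocation.

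n per arm = 2 × (1.960 + 0.842)² × 6² / 2.4² = 98.1, rounded up to 99. The t-test solution is 99.08. With 20% attrition, 99 / 0.8 = 123.75, rounded up to 124 per arm, 248 in total. The plan's figures are reproduced.

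**2. How many can be left out without imputation.** At exactly 20%, 248 × 0.20 = 49.6, or about 50 participants, leaving about 99 per arm (124 × 0.8 = 99.2).

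**3. Bias of the complete-case contrast.** Let m be the proportion missing in an arm and k the amount by which completers' mean AUDIT reduction exceeds that of participants lost.

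- True arm mean reduction = (1 − m) × completers' mean + m × (completers' mean − k) = completers' mean − m × k.
- So the complete-case mean overstates the arm's reduction by m × k.
- With the same k in both arms, the bias in (Remote reduction − Standard reduction) is k × (m_Remote − m_Standard).

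Neither the two values of m nor k is in the documents. All values below are **assumptions**.

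| Missing, Standard / Remote | Overall | k | Bias (points) | Share of 2.4 |
|---|---|---|---|---|
| 20% / 20% | 20% | any, equal by arm | 0 | 0% |
| 25% / 15% | 20% | 3 | −0.3 | 13% |
| 25% / 15% | 20% | 4 | −0.4 | 17% |
| 25% / 15% | 20% | 5 | −0.5 | 21% |
| 15% / 5% | 10% | 3 | −0.3 | 13% |

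The last row shows that lower overall attrition does not in itself remove the problem: the bias depends on the 10-percentage-point difference. Equal rates do not guarantee zero bias either. With 20% missing in both arms, k = 0 in Remote and k = 3 in Standard, the bias is 0.20 × 0 − 0.20 × 3 = −0.6.

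**4. What that does to the test.** With 25% / 15% missing, the numbers analysed are 124 × 0.75 = 93 in Standard and 124 × 0.85 = 105.4 in Remote. SE = 6 × √(1/93 + 1/105.4) = 0.854. Normal approximation:

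- Bias −0.3 (k = 3): power at a true 2.4 = Φ((2.4 − 0.3)/0.854 − 1.96) = about 69%, against about 80% without bias.
- Bias −0.5 (k = 5): Φ((2.4 − 0.5)/0.854 − 1.96) = about 60%.
- Opposite direction, bias +0.3 with no true difference: the chance of declaring Remote superior = 1 − Φ(1.96 − 0.3/0.854) = about 5.4%, against 2.5%.

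**The case against.** The other side has several good points, and they limit what can be claimed.

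- **The arms differ in sessions, not in assessments.** Follow-up has the same schedule in both arms and is done by blinded assessors. The 8-week window runs from 6 to 16 weeks. Section {18b} allows the self-report measures by telephone, collects two secondary contacts and compensates attendance. Missing a session removes nobody from the primary analysis. This stands: differential loss is possible, not shown.
- **Bias is conditional.** A reader might infer that the result will be biased. The documents do not support that, since complete-case analysis is biased only if loss relates to outcome, given the model covariates, in a way that does not cancel between arms.
- **Direction.** A reader might infer that the plan favours the new intervention. On the argument about attendance burden it does the reverse: Standard would lose more poor responders and look better than it is, costing Remote power.
- **Choice of method after seeing the data.** A reader might infer this from the conditional rule. It is not supported: the rule is pre-specified, depends on attrition and not on outcomes, and section {17a} keeps the statistician blinded to arm until the dataset is closed.
- **What anticipated means.** Figures of roughly 10%, below 10% and 20% all appear, but 20% is the natural reading because section {20c} ties it to the power analysis. Stating the number would settle it.
- **Intention-to-treat.** The protocol's gloss concerns treatment completion, and the restriction to observed scores is stated openly. Analysis as randomised is kept for those observed. The tension is only with the word all.
- **Secondary mixed model.** It might seem that this already supplies an all-visits estimate at 8 weeks. Section {20a} names AUDIT at 20 and 32 weeks for it; the 8-week visit is named for PEth.

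What none of this answers is why the remedy for missing outcomes should depend on overall attrition, or why nothing examines them below that level.

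**Conclusion.** The point holds in a limited form. The primary analysis excludes everyone without an 8-week AUDIT, imputation depends on overall attrition alone, and no planned sensitivity analysis addresses missing outcomes. At or below 20% attrition, loss that relates to outcome and differs by arm can bias the primary contrast uncorrected.

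The illustrative size is 0.3 to 0.5 AUDIT points, 13% to 21% of the target difference. It rests wholly on assumed values: 25% versus 15% missing and a gap of 3 to 5 points, the same in both arms. More extreme splits give larger figures, but nothing in the documents makes them likely, given the attrition of about 10% in the team's earlier trials. These numbers show what the rule would let through; they do not predict this trial's bias. This should be corrected, but it does not undermine the design: the sample size is unaffected.

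**What to change.** Remove the attrition trigger from section {20c} and the restriction to 8-week completers from the primary analysis in section {20a}. Whatever the attrition, take the primary 8-week contrast from one pre-specified method:

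1. multiple imputation, done separately by arm, for all randomised participants, using baseline AUDIT and the 20- and 32-week AUDIT; or
2. a repeated-measures model of AUDIT at 8, 20 and 32 weeks with baseline AUDIT, the stratification factors, visit and arm-by-visit, reporting the 8-week arm difference.

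The second option uses participants who miss week 8 but return later. With baseline as a covariate, it does not include those with no follow-up AUDIT at all; the first option does.

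Keep the complete-case regression as a sensitivity analysis. Both options assume data missing at random, so neither would by itself remove the not-at-random bias illustrated above. Add a delta-adjusted sensitivity analysis in which missing participants do worse by a stated amount, varied separately by arm, and report how large that amount must be to change the conclusion.

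The cost is revised wording and some extra analysis. AUDIT is already collected at every timepoint (section {18a}), so no new data or participants are needed.
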